#### Inclusion criteria

ICU patients with decisional capacity, who can give informed consent for study participation, and incapacitated patients with an available, legally recognised, substitute decision-maker able to provide informed consent on their behalf.Adults aged 18 years and more.The leading cause of critical illness is not cancer; such patients represent a clinically distinct group with different prognosis, pre-existing PC involvement and oncology-specific care pathways that would likely confound the trial’s effect on ICU LOS and other outcomes.^26 27^ Moreover, the most significant evidence gap in the literature on PC for critically ill patients concerns non-cancer populations,^26^,^28^ providing a strong rationale for the inclusion criterion and the design of the present trial.New admission in the participating ICU, with LOS of >72 hours.Need for specialised PC according to attending physician judgement, based on (a) significant disagreement among ICU team members and/or family members about appropriateness of ICU treatment intensity or (b) consideration of therapy limitations or (c) expected benefit from specialised PC consultation for the patient/family and/or ICU team members.

#### Exclusion criteria

Moribund patients expected to die within 24 hours.

### Study procedures

Each participating ICU cluster goes through the below-described consecutive phases.

### Observation phase: control condition

The care and treatment of the patient is carried out in the participating ICU according to local standards of care. If patients require specialised PC, and this is available, it is provided in person according to local practice.

### Crossover phase: clinician education, bedside tools and interventionist training

In the crossover month, the Interdisciplinary Center for Palliative Medicine of the University Hospital Duesseldorf, Germany, provides a structured training programme to the physicians and nurses in the respective satellite ICUs (programme description available at https://clinicaltrials.gov/study/NCT06425692?term=enhancing-palliative-care-&rank=2). Training in PC is carried out online in a blended learning format^29^ with an interactive e-learning course and interactive webinars.^30^ Training impact is assessed by comparative self-assessment^31^ to assess predefined learning gains, and by the continuing professional response questionnaire,^32^ a validated tool to identify behavioural change. Training participation rate is determined as the ratio of the actual number of participants to the total number of eligible staff members of the participating ICUs.

Additionally, a newly developed checklist of possible trigger factors (box 1) is provided to the ICU staff to raise awareness for PC needs of ICU patients and their families daily and guide the tele-PC consultations. The checklist is based on literature research and developed by the Delphi process among participating clinicians of the EPIC consortium. An additional bedside tool is a factsheet with recommended PC practices and relevant legislation developed for this study by the department of intensive care medicine of the National and Kapodistrian University of Athens, Greece.

Box 1Trigger checklist for palliative care needs for intensive care unit patients and their familiesFrequent hospitalisations/emergency department visitsPersistent/uncontrolled symptomsExplore patients’ values and preferences and align the careAssistance with ascertaining goals of care or end-of-life planningPatient/family request for palliative care involvementExistential distress or spiritual concerns

The EPIC interventionists (PC consultants) in each hub who provide the teleconsultation have received a variable range of PC education and therefore will receive structured training to ensure a standardised approach according to current standards^25^ (box 2). Training impact is assessed by pretraining and post-training evaluations, using feedback surveys. Intervention fidelity is assessed by periodic (quarterly) audits of consultations, adherence to the protocol and clinician self-reports as described in further detail below.

Box 2Key components of EPIC tele-interventionist trainingAsynchronous training (part 1 and 2)—recorded PowerPoint presentationsSynchronous training (booster sessions)Monthly online meetingsIdentifying areas of specific need and addressing themSkill practiceDebriefingEvaluationContent: part 1The EPIC 6-item checklistUnderstanding diagnosis, treatment and prognosisPrognostic awareness (hopes and worries technique)Empathetic statementsDelivering serious newsConflict de-escalation techniquesContent part 2Distressing symptomsAppropriateness of care conceptGoals of care frameworkReframe and focusing on current realityMapping values and prioritiesAligning care with patient preferencesPlanning future care/dischargeSpecific situationsSpiritual injury and the ‘miracle talk’EPIC, Enhancing Palliative Care in the Intensive Care Unit.

PC trigger checklist and PC consultants’ training are part of the study contribution of the department of palliative medicine at the General University Hospital of Prague, Czech Republic.

### Implementation support and fidelity monitoring

Measures to support implementation include:

Identification of local champions (eg, prestigious senior physicians or clinical researchers): these key facilitators support smooth communication between PC specialists and ICU teams, ensuring compliance and engagement.Personal introductory meetings (organised by country-level lead investigators): during the 4-week crossover period, PC specialists meet with ICU clinicians, staff and local champions to build trust and promptly identify potential challenges in protocol implementation, thereby promoting protocol adherence.^33^Legal framework factsheets: developed by EPIC researchers, these concise materials outline national laws relevant to end-of-life care, providing ICU-specific infographics.Communication skills handouts: ICU staff receive practical guides, covering essential topics such as delivering bad news and shared decision-making.Ethical practice prompts: during consultations, teams receive structured reminders to integrate ethical screening into PC discussions.

To ensure intervention fidelity, a three-step plan is implemented:

#### Training and ongoing supervision

EPIC consultants receive the comprehensive training mentioned above and presented in box 2.

#### Monitoring and documentation

Biweekly ICU screening/enrolment reports (provided by investigators during country-level and/or trial steering committee conference calls) detail the total number of enrolled patients, while monthly updates ensure timely data sharing for streamlined oversight.

#### Feedback and support

Feedback loops reinforce protocol adherence, supported by the aforementioned status updates from national coordinators and their associates. Furthermore, at each PC consultation, specialists review screening status, ensuring questionable cases are addressed.

National coordinators continue fostering strong partnerships across all study levels. Identified challenges are resolved through direct communication with clinicians or targeted protocol adjustments. These developments are discussed in three-monthly conference calls of the General Assembly/Executive Board.

### Outcome measures

#### Primary outcome

The primary outcome is the ICU LOS in days, operationalised as the total number of consecutive and/or non-consecutive ICU days from the start to the end of an index hospitalisation at a study-participating hospital; any transfer to another hospital for treatment continuation signifies termination of the index hospitalisation, and therefore, any subsequent ICU admission cannot contribute to the measured ICU LOS. Regarding index hospitalisation, whenever ICU discharge is followed by ICU readmission on the same day, ICU LOS is determined by taking into account the aforementioned day only once (rather than two times).

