## Methods

### Overview

We intend to complete a controlled, cluster-randomised, non-blinded stepped-wedge design trial with crossover phase to compare the intervention with standard treatment. Each cluster is formed by all participating ICUs sharing staff within one building or healthcare institution. Standard treatment is provided during the observation phase and the intervention is delivered during the subsequent intervention phase. All ICUs start with the observation phase. All patients who fulfil the eligibility criteria, including the ICU physician’s assessment of the need for specialised PC, are asked to participate in the study. At a randomised time point, each ICU cluster enters a crossover period of 1 month (see online supplemental material figure 1). Within this month, ICU staff receive online training in basic PC and EPIC interventionists are trained to conduct telepalliative consultations. In the subsequent intervention phase, the ICU physicians can use a newly developed checklist to assess specialised PC needs and schedule at least one specialised PC consultation via telemedicine. Survivors’ and relatives’ outcomes are gathered at pre-specified time points, that is, on ICU/hospital discharge and during a 3-month follow-up interview. Clinician outcomes (concerning burnout, end-of-life practices and ethical decision-making) are collected through a dedicated survey scheduled repeatedly in the control and intervention periods. The trial design is illustrated in figure 1.

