#### Participant timeline

The data collection timeline is represented in table 8. The collection of secondary outcomes throughout follow-up is also performed for patients who have died before its completion time point (ie, at 3 months after ICU discharge), as applicable.

**Table 8 T8:** Summary presentation of data collection schedule

	Visit 1 study inclusion	Visit - teleconsultation	Visit 2 ICU discharge*	Visit 3 follow-up 3 months post-ICU discharge	
Control phase (CP) Intervention phase (IP)	CP/IP	IP	CP/IP	CP/IP	
Time (hours; days (d))	Any time after 72 hours	<48 hours after inclusion		28 d after ICU discharge (retrospective)	90 d after ICU discharge
Review of inclusion and exclusion criteria, medical history	x				
Information/declaration of consent by legally recognised, substitute decision-maker	x				
Information/declaration of consent by patient	x				
Primary endpoint (ICU length of stay)	x		x		
Secondary endpoints	x	x	x	x	x
Mortality	x	x	x	x	x

* Defined as the last day of ICU stay (ie, the day of occurrence of ICU discharge that is not followed by any ICU readmission during the index hospitalisation); in case of more than one ICU admission during the index hospitalisation, the data on secondary endpoints are (repeatedly) collected on the corresponding days of ICU discharge; however, only the data collected on the last one of the aforementioned ICU discharge days are included in the secondary endpoints’ analyses.

ICU, intensive care unit.

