#### Data analysis plan

A detailed Statistical Analysis Plan will be finalised before database lock. The analysis of the data will begin with a detailed statistical description of the study sample, differentiated by control and intervention phase. Categorical characteristics will be summarised using absolute and relative frequencies. For ordinal or metric non-normally distributed data with up to five categories, we will present the absolute and relative frequencies, along with the median and the IQR. For data with more than five categories, only the median and IQR will be reported. For metric data that follows a normal distribution, we will present the mean value, accompanied by the SD and the 95% CI.

All analyses will be conducted on an intention-to-treat basis, with the patient representing the unit of analysis. We will use generalised linear mixed models (GLMMs) for continuous outcomes,^23 35^ accounting for the clustered data structure, to compare the primary endpoint between the control and intervention phases. Sensitivity analyses will include additional adjustment for ICU mortality.

Predefined subgroup analyses will be conducted to explore the heterogeneity of the treatment effect in patients concerning sex, religiosity, socioeconomic parameters and educational level. In addition, treatment effects will be compared between ICUs with high-tech versus low-tech telemedicine consultations, with good versus average or poor ethical climate, and ICUs with and without pre-existing palliative counselling. Further comparisons will be made among participating countries, patients with an ICU stay at enrolment of less than 5 days versus at least 5 days, and patients with versus without decisions to limit treatment at enrolment.

Subgroup analyses and analyses of all secondary endpoints will be considered as exploratory. Statistical testing will be carried out at a two-sided significance level of 5%. For the primary hypothesis, no correction for multiple testing is necessary.

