## Discussion

The EPIC study is the first to investigate the impact of early integration of consultative PC in multidisciplinary European ICUs via telemedicine and an educational programme for ICU staff, implying a system-based harmonised practice model. The complex intervention fosters interdisciplinary collaboration and is assessed against standard care, with outcomes spanning patient clinical trajectories, family and clinician perceptions, and economic endpoints. Potential limitations include heterogeneity in ‘usual care’ across sites, subjectivity in trigger-based inclusion criteria, and the practical challenges of collecting patient-reported or proxy-reported data under high stress. In balancing feasibility with the high-quality analytic need to capture EQ-5D-5L data at five follow-up time points, we opted for two additional retrospective assessments as illustrated in figure 1. Intervention fidelity is monitored quarterly (every 3 months) via audits specified in our Implementation support and fidelity monitoring plan (see Methods), during which teleconsultation logs, trigger-checklist adherence and any relevant clinician comments (listed in the e-CRF) are reviewed.

Tele-PC consultations address a critical gap in ICUs by extending specialist expertise to units without onsite PC teams.^21^ Leveraging secure audio-visual platforms, EPIC enables timely symptom assessment, shared decision-making and goal clarification without in-person referral delays. During the COVID-19 pandemic, tele-PC maintained high clinician satisfaction and family engagement under visitor restrictions.^20^ By placing PC experts virtually at the bedside, EPIC overcomes geographic barriers and promotes consistent care delivery across diverse centres.^19^

Successful teleconsultation depends on structured implementation and robust training. EPIC’s blended-learning curriculum—interactive e-modules and live webinars—equips ICU teams with core palliative skills and the six-item trigger checklist for early need identification.^28^ Quarterly fidelity audits, empowered local ‘champions’ and clear standard operating procedures ensure adherence to EPIC’s protocol. This mirrors best practices from recent ICU palliative trials, which highlight the necessity of defined workflows, continuous feedback loops and sustained support to embed practice change.

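### Earlier recognition of palliative care need in the intervention phase can enrol short ICU stays that the control phase misses, so mean ICU LOS can fall with no treatment effect

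*Protocol article*

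**What the plan says.** All from the protocol article:

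- **Outcome.** Under Primary outcome, ICU LOS is "operationalised as the total number of consecutive and/or non-consecutive ICU days from the start to the end of an index hospitalisation". Days before enrolment count.
- **Entry.** Inclusion criteria require "New admission in the participating ICU, with LOS of >72 hours" and "Need for specialised PC according to attending physician judgement". Table 8 places study inclusion at "Any time after 72 hours". Patients are therefore enrolled when need is recognised, on no fixed ICU day.
- **What changes at crossover.** Staff are trained in the crossover month. The Overview says: "In the subsequent intervention phase, the ICU physicians can use a newly developed checklist to assess specialised PC needs". The Crossover phase section gives the checklist's purpose as "to raise awareness for PC needs of ICU patients and their families daily", and the Discussion calls it "the six-item trigger checklist for early need identification".
- **Safeguards.** Eligibility criteria states that enrolment criteria are the same in both phases and that consecutive admissions are screened. The strengths and limitations box concedes that the need criterion is partly subjective.
- **Analysis.** The Data analysis plan compares the phases with a mixed model. The one sensitivity analysis it names adjusts for ICU mortality. Enrolment timing appears only in an exploratory subgroup: "patients with an ICU stay at enrolment of less than 5 days versus at least 5 days".

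**The concern.** To be analysed, a patient must still be in the ICU when need is recognised. Slow recognition in the control phase loses patients who leave the ICU, alive or dead, before anyone identifies them, so the enrolled control sample is weighted towards long stays. Faster recognition in the intervention phase lets some of those short stays in. Mean LOS among enrolled patients then drops through selection alone.

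Randomising the crossover date does not prevent this, because the selection happens after allocation, in an unblinded trial, through a judgement that the intervention is meant to change. Month effects in the model do not remove it either, because the shift coincides with the change of phase in each cluster. At stake is whether a significant reduction in the only confirmatory endpoint can be attributed to the intervention.

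**Working it through.** **1. The plan's own figures.** 23 ICUs × 87 patients = 2001, as stated. A standard stepped-wedge variance calculation (23 clusters, 34 recruiting months, 87/34 = 2.56 patients per month, ICC 0.01, SD 9, difference 2 days, one cluster crossing per month in months 7 to 29) gives 83.7% power with categorical month effects and 85.2% with a linear trend. This agrees with the stated 85%. The step chart is not shown, and other assumed schedules gave about 72% to 93%. The power figure is not in dispute. It is used only to obtain a standard error.

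**2. Implied standard error.** SE = 2 / (z for 0.975 + z for power).
- 85% power: 2 / (1.960 + 1.036) = 0.667 days.
- 80% power (the figure given after the July 2025 change): 2 / (1.960 + 0.842) = 0.714 days.

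**3. The mechanism by hand.** Suppose stay beyond 72 hours is exponential with mean 4.5 days. Patients enrolled at day 5 have mean LOS 5 + 4.5 = 9.5. Patients enrolled at day 4 have mean LOS 4 + 4.5 = 8.5. The share of eligible stays still in the ICU is exp(-2/4.5) = 0.64 at day 5 and exp(-1/4.5) = 0.80 at day 4. No stay has changed, but more of the short ones are in the sample.

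**4. Simulation with no treatment effect, calibrated to the protocol.** LOS = 3 days plus a lognormal. Recognition occurs at 3 days plus an exponential delay. A patient is enrolled if still in the ICU at that time. Stays are calibrated so that enrolled control patients have mean 9 and SD 9, the protocol's planning values. The delays are assumptions. False-positive rate = P(|Z| > 1.96), where Z has mean bias/SE.

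| Mean delay, control → intervention (days) | Eligible stays enrolled | Mean enrolment day | Difference in total LOS (days) | False positives, SE 0.667 / 0.714 | Difference in days after enrolment |
|---|---|---|---|---|---|
| 1 → 0.5 | 82% → 92% | 3.79 → 3.44 | -0.50 | 12% / 11% | -0.16 |
| 2 → 1 | 61% → 76% | 4.23 → 3.74 | -0.83 | 24% / 22% | -0.35 |
| 3 → 1.5 | 46% → 62% | 4.51 → 3.95 | -0.99 | 32% / 28% | -0.43 |

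Restricted to the patients whom the control phase would also have enrolled, the difference is 0.00 in every row. A harsher assumption, cutting the delay to a quarter, gives -0.76, -1.36 and -1.68 days.

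**5. Other stay distributions (gamma), no treatment effect.**
- Delay 1 → 0.5: -0.38 to -0.61 days.
- Delay 2 → 1: -0.57 to -0.93 days.
- Delay 3 → 1: about -1.0 day for an exponential stay (control mean 9.3), and -1.5 to -1.6 for more skewed stays (control means 11.2 and 11.6, above the protocol's 9).

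**6. Recognition time correlated with stay.** For correlations from -0.5 to +0.5 (control mean about 8 to 10 days, SD about 8 to 9), the difference in total LOS stayed between -0.3 and -1.5 days. Together with step 5, the range is about -0.3 to -1.6 days. At SE 0.667, a bias of 0.3 gives Z a mean of 0.45 and about 7% false positives. A bias of 1.6 gives a mean of 2.40 and about 67%.

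**7. How candidate analyses behave.**
- *Days after enrolment:* smaller bias than total LOS in every scenario run, but not zero.
- *Delayed-entry analysis:* with recognition independent of stay, the 60-day restricted mean was 6.41 in both phases against a true 6.40.
- *Adjustment for enrolment day (delay 3 → 1):* 0.00 to -0.06 days if recognition is independent of stay. With a spline at correlation -0.3 the bias was about -1.2 to -1.35, and at +0.3 about +1.1 to +1.3. At -0.5 it was about -2.1 to -2.3, and at +0.5 about +1.9 to +2.15.

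**The case against.** The strongest case against the point is this. The criteria are identical, all consecutive admissions are screened in both phases, and screening and enrolment are reported every two weeks. Physicians may use the checklist but need not, and its items are not the enrolment criteria. No time to enrolment is given, so the size is unknown, and even the direction depends on which extra patients are recognised. The article defers detail to a statistical analysis plan that is not shown, so the covariates of the primary model are unknown. Total LOS also matches the stated hypothesis and captures any effect of staff training before enrolment.

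Most of this stands as a limit on size. It does not remove the mechanism: identical criteria do not give identical enrolment when the criterion is the judgement being trained, and the two analyses named that come nearest do not address it. Adjusting for ICU mortality concerns another variable. The 5-day subgroup is exploratory and splits on something the intervention can shift.

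A reader might infer four stronger points that the documents do not support:
- *That counting pre-enrolment days is itself the error.* It is not. Enrolling the same patients earlier changes nothing, and starting the clock at enrolment leaves some bias. The cause is who gets enrolled.
- *That each day of earlier enrolment shows as one day of reduction.* This holds only if remaining stay does not depend on enrolment day.
- *That the bias matches the 2-day target.* Under the main assumptions it reaches about 1.6 days, and the largest values come with control means above 9 or with severe cuts in delay.
- *That LOS adjusted for enrolment day should become the primary analysis.* Step 7 shows that this can leave, reverse or enlarge the bias when recognition depends on stay, which is plausible for a clinical judgement.

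**Conclusion.** The concern holds as a selection risk on the primary comparison. The protocol ties entry to a judgement that the intervention is designed to bring forward, and analyses only patients still in the ICU at that moment. In every scenario run in which the recognition delay fell, the spurious difference favoured the intervention: about -0.3 to -1.6 days, or 15% to 80% of the 2-day target (0.3/2 to 1.6/2), with false positives of about 7% to 67% at SE 0.667.

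These figures rest on assumed falls in mean delay (1 to 0.5 days, up to 3 to 1 day), assumed stay distributions, and extra enrolments drawn from the same eligible population. They are a range and not an estimate. The bias is zero if recognition timing and the enrolled set do not differ by phase. The documents do not show that the trial will be biased, nor that a positive result would be uninterpretable whatever the enrolment data show.

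**What to change.** Keep total ICU LOS as the defined endpoint. Before database lock, add to the Data analysis plan these prespecified sensitivity analyses of the primary comparison:

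1. ICU days after enrolment.
2. A delayed-entry (left-truncated) analysis of LOS, with entry at enrolment.
3. Total LOS adjusted for ICU day at enrolment, as a spline.

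State that analyses 2 and 3 assume recognition time is independent of remaining stay given covariates, and show results under departures from that assumption. Report ICU day at enrolment and enrolled/screened counts by phase. State in advance that a LOS reduction will be attributed to the intervention only if it is consistent across these analyses, or if enrolment timing and the enrolled fraction do not differ by phase. Do the same for days of ventilation, renal replacement and other organ support.

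The cost is modest. It means extra wording and analyses, using admission and enrolment dates the trial needs anyway and the screening reports already planned. The downside is that the post-enrolment analyses leave out any effect of ICU-level training before enrolment, which is one reason to keep total LOS as the endpoint.
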